**Methods/design:**

EPD is a parallel group, double-blind, randomized controlled trial. Community-dwelling volunteers aged 50 years or more are being recruited from different community centers and screened for eligibility. Enrolled subjects are being divided in 3 groups: a) without subjective or objective cognitive impairment, b) with subjective memory complaints, and c) with mild cognitive impairments. Participants in each group (at least 180) are being randomly assigned (1:1) to an experimental group, performing a supervised training including aerobic and resistance exercises of moderate/high intensity, or to a control group. Primary outcome will be 48-months changes in Mini Mental State Examinations. Secondary outcomes will be changes in several cognitive tests including a composite cognitive score. Time points will be at baseline, and at 6, 12, 24, 36 and 48 months. Statistical analysis will be done as intention to treat, complete case and mixed model analysis.

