### Sample size calculation

Sample size calculations were based on the findings of previous studies and were performed separately for each category group. For heathy group, considering that MMSE scores decline 0.3 points in 4 years, we considered 0.6 points the minimal clinically important difference and used a Standard Deviation (SD) of 1.2 [38]. For SMC group, since that annual decline in MMSE score vary between 0.46 and 1.32 and that SD may vary between 1.48 and 2.6 [39], we considered 1.3 points the minimal clinically important difference and used a SD of 2.6. For MCI group, considering that the annual decline in MMSE score vary between 0.1 and 1.1 [40] and that SD may vary between 0.3 and 3.2 [41], we considered 1.6 points the minimal clinically important difference and used a SD of 3.2. Considering the percentage of drop-outs in previous similar studies and the length of the present study, we assumed a 30% attrition rate. Using an α level of less than 0.05, 90 participants per arm group will guarantee a power of 0.80.

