### Randomization

After the baseline assessment, the participants of each category groups A, B and C were randomly assigned to one of the two groups (CG and EG) by using 1:1 blind randomization. For the randomization, a scheme generated via a computerized random number generator was used.

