### Statistical analysis

Data will be analysed using the SPSS statistical software package (IBM, v.20.0, Chicago, IL, USA). Variables will be examined for outliers and extreme values by means of box and normal quantile-quantile plots, Shapiro-Wilk’s and Kolmogorov-Smirnov’s tests. When normal distribution cannot be accepted, the transformed variable (square, square root, logarithmic, reciprocal of square root or reciprocal transformations) will be reviewed. For normally distributed continuous variables, arithmetic means and SDs will be calculated, while for not normally distributed continuous variables, median, 25th and 75th percentiles will be calculated, according to the shaped distributions of two groups, as assessed by visual inspection of population pyramids. Sampling homogeneity (or baseline differences between groups) will be examined by means of chi-square (χ^2^) for categorical variables, independent-samples t-test for normally distributed variables and Mann-Whitney U test for not normally distributed variables. Differences between groups (experimental group vs. control group) and changes in the cognitive performance during the trial will be evaluated by means of Repeated Measures Analysis of Covariance (RM-ANCOVA) in the intention to-treat and complete-case analyzes, or with Linear Mixed Model analysis (LMM). The evaluations in the different time-points will be considered as the within-subjects factor whereas the two groups will be considered as between factor. Age, education level and gender will be included as covariates. The assumptions of equality of variances and sphericity will be assessed by means of Levene’s test and Mauchly’s test, respectively. The Greenhouse-Geisser or the Huynh-Feldt correction will be applied if the assumption of sphericity will be violated. Post-hoc independent-samples t-test will be performed to detect significant differences among trial conditions.

A *p*-value < 0.05 will be considered statistically significant.

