Nevertheless, despite the increasing interest on the exercise effects on brain health, some authors claimed that the protective effects of exercise on dementia or cognitive impairment may be overvalued [56, 57]. Also, previous studies showed overall that physical fitness levels are not strongly correlated with cognitive performance [58]. This discrepancy in author opinions and results suggests that further high-quality studies, and interventional studies including long follow-up periods and high reproducible exercise interventions, are necessary.

The EPD trial will: (a) evaluate the effectiveness of multimodal exercise program of 48 months in improving neurocognitive functions in individuals aged 50 years or older at different risk of AD; (b) identify the category of subjects and the cognitive function that gets the best benefits from such modality of exercise; c) examine the possible mechanisms by which exercise improve cognition.

In conclusion, this study, if successful, may represent an affordable and safe method to demonstrate that exercise represents a protective tool to delay the onset of dementia and the cognitive impairment in older adults at risk, such as subjects with SMC or MCI. Results of this study are expected to have important public health implications and a profound impact on future AD prevalence.

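### The stated model never compares the exercise effect between categories A, B and C, although the trial promises to find which category benefits most

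*Protocol article*

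**What the plan says.** The Discussion lists three things the trial will do. The second is to "identify the category of subjects and the cognitive function that gets the best benefits from such modality of exercise".

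The design is built around the categories. Under Randomization, "the participants of each category groups A, B and C were randomly assigned to one of the two groups (CG and EG"), and the abstract gives the size: "Participants in each group (at least 180) are being randomly assigned (1:1"). Under Sample size calculation, the computations "were performed separately for each category group", each with its own effect and SD.

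The model is set out under Statistical analysis, as RM-ANCOVA or a linear mixed model: "The evaluations in the different time-points will be considered as the within-subjects factor whereas the two groups will be considered as between factor". The same paragraph defines these two groups as experimental and control, and names age, education level and gender as covariates. Category A/B/C is not given as a factor, covariate, interaction or stratum of analysis. Post-hoc independent-samples t-tests follow, and nothing says that they contrast arm effects across categories. One threshold applies throughout: p below "0.05 will be considered statistically significant".

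**The concern.** To say that one category benefits more than another is a claim about a difference between two arm effects. It needs an estimate of that difference with its own standard error. The model as written has no parameter for it.

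This holds on either reading of the section. If all participants go into one model, it yields a single arm effect and nothing by category. If the model is run three times, it yields three arm effects, each compared with zero and none compared with another. The readily available summary is then which categories reached significance, and that pattern is not evidence that the effects differ. At stake is a conclusion about whom exercise helps (healthy people, those with memory complaints, or those with MCI), to which the article attaches public health importance.

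**Working it through.** **Inputs, from Sample size calculation.** Category A: "we considered 0.6 points the minimal clinically important difference and used a Standard Deviation (SD) of 1.2". Category B: "we considered 1.3 points the minimal clinically important difference and used a SD of 2.6". Category C: effect 1.6, SD 3.2. Alpha 0.05, power 0.80, attrition 30%, 90 per arm in each category. Sidedness is not stated; two-sided is assumed.

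**Step 1: reproduce the plan's figure.** The standardised effect is 0.6/1.2 = 1.3/2.6 = 1.6/3.2 = 0.5 in every category.
- n per arm = 2 × (1.960 + 0.842)² / 0.5² = 62.8, so 63.
- 63 / (1 − 0.30) = 90, which matches.
- A one-sided test needs 50 before attrition and does not match.

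The stated power therefore covers the arm comparison within one category and nothing else.

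**Step 2: what three separate tests would show if the effects were identical.** With 63 completers per arm and d = 0.5, the t-test has power 0.795. The categories contain different people, so the three tests are independent.
- All three significant: 0.795³ = 0.502.
- None significant: 0.205³ = 0.009.
- Mixed: 1 − 0.502 − 0.009 = 0.489, about 49%.

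About half the time, identical standardised effects would look like a difference between categories.

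**Step 3: power of the comparison that aim (b) needs.** The planning effects are taken as true, in MMSE points, with 63 completers per arm. The variance of each category's arm contrast is 2 × SD² / 63:
- A: 2 × 1.44 / 63 = 0.0457
- B: 2 × 6.76 / 63 = 0.2146
- C: 2 × 10.24 / 63 = 0.3251

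For each pair, SE = √(sum of the two variances). Power is from the two-sided z test, and the last column is (1.960 + 0.842) × SE.

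| Pair | Planned difference in effect | SE | Power | Difference detectable at 80% power |
|---|---|---|---|---|
| A–B | 0.7 | 0.510 | 28% | 1.43 |
| A–C | 1.0 | 0.609 | 38% | 1.71 |
| B–C | 0.3 | 0.735 | 7% | 2.06 |

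Global 2-df test: the inverse-variance weights are 21.88, 4.66 and 3.08, and the weighted mean effect is 0.814. The noncentrality is 21.88 × (0.6 − 0.814)² + 4.66 × (1.3 − 0.814)² + 3.08 × (1.6 − 0.814)² ≈ 4.00, which gives power of about 42%.

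**Step 4: the scale matters.** In SD units all three planning effects equal 0.5, so the planned interaction is zero on that scale. For one category at 0.5 SD and another at 0, SE = √(4/63) = 0.252 and power is about 51%.

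**The case against.** The strongest reply is that this is mostly silence. The article never says the categories are pooled and never rules out an interaction, and an unseen analysis plan may contain one. The ranking of categories appears in one Discussion sentence and not among the aims in the abstract or Background. What stands of this: the point is narrow, and labelling the ranking exploratory would go a long way. But the article states its model down to covariates and sphericity corrections, and it says the trial will deliver this result. That is a mismatch between two stated things, not a missing detail.

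Several stronger readings are tempting, and the documents do not support them.

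- *The analysis pools the categories and mixes SDs of 1.2, 2.6 and 3.2.* Separate randomisation and separate sample sizes make three parallel analyses the likelier intention.
- *The best category will be picked by p-value.* No section says so; estimates with intervals are equally compatible. The 49% shows why a significance pattern must not be used. It is not a forecast of what the investigators will do.
- *Three unadjusted tests (1 − 0.95³ = 14.3%) require a Holm correction.* Each category is a separately powered population with its own hypothesis, so adjustment across them is debatable.
- *A false claim is near certain across the cognitive battery.* For about 10 outcomes in 3 categories, 1 − 0.95³⁰ = 79%. That assumes independence between tests taken on the same people and no effect anywhere. All but the MMSE are declared as secondary or further outcomes.
- *A pooled overall test should come first.* This is a real trade-off. If only MCI participants benefit (1.6 points), the pooled test has power 0.55 with equal weights, 0.37 on the SD-standardised scale, or 0.15 with inverse-variance weights. The design gives the MCI comparison itself about 0.80.

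**Conclusion.** The point holds in this form: the question of which category benefits most is not answered by the stated analysis. A reader might infer that it cannot be answered at all. That goes too far, because the randomised groups allow the contrast to be estimated, only with low power: about 42% globally and 7% to 38% pairwise under the article's own planning values.

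The within-category comparisons are unaffected; 90 per arm reproduces exactly for them.

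The figures assume a two-sided 0.05, 63 completers per arm in each category, and that the planning SDs apply to the 48-month MMSE change. The 49% also assumes a true effect of exactly 0.5 SD in every category.

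**What to change.** In Statistical analysis:

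1. Include category, the randomisation stratum, in the model with arm-by-category and arm-by-category-by-visit terms, and with residual variance estimated separately by category. The linear mixed model already listed can carry this; RM-ANCOVA assumes a common covariance structure. If three separate analyses are preferred, their estimates are independent, so each difference in effect has SE equal to the square root of the summed squared SEs.
2. Keep the within-category 48-month MMSE contrasts, which are what the sample size supports.
3. State that any claim about which category benefits more rests only on the arm-by-category contrast at 48 months, in MMSE points, with its confidence interval, and not on which categories reach significance.
4. Label the ranking of categories and of cognitive functions exploratory, and report the limited power given above.

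The cost is wording and analysis work. No participants, visits or measurements are added, and power for the within-category comparisons is not given up. Resolving the planned differences at 80% power is out of reach by design: it would take 263 (A–B), 184 (A–C) or 2966 (B–C) completers per arm.

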## Data Availability

Not applicable.

## Abbreviations

AAHPERD: American Alliance for Health, Physical Education, Recreation, and Dance
AD: Alzheimer’s Disease
CDR: Clinical Dementia Rating
EPD: Exercise for Prevention of Dementia
FAB: Frontal Assessment Battery
GDS: Geriatric Depression Scale
MAC-Q: Memory Complaint Questionnaire
MCI: Mild Cognitive Impairment
MMSE: Mini- Mental State Examination
PASE: Physical Activity scale for the Elderly
PMT: Prose Memory Test
RAVLT: Rey’s Auditory Verbal Learning Test
RCT: Randomized Controlled Trial
SD: Standard Deviation
SF-36: Short-form Health Survey
SMC: Subjective Memory Complaints
TMT: Trail Making Test
